## Abstract

**Background:**

More than half of the patients with type 2 diabetes (T2DM) patients are diagnosed with one or more comorbid disorders. They can participate in several single-disease oriented disease management programs, which may lead to fragmented care because these programs are not well prepared for coordinating care between programs. Comorbid patients are therefore at risk for suboptimal treatment, unsafe care, inefficient use of health care services and unnecessary costs. Case management is a possible model to counteract fragmented care for comorbid patients. It includes evidence-based optimal care, but is tailored to the individual patients' preferences.

The objective of this study is to examine the effectiveness of a case management program, in addition to a diabetes management program, on the quality of care for comorbid T2DM patients.

**Methods/Design:**

The study is a randomized controlled trial among patients with T2DM and at least one comorbid chronic disease (N = 230), who already participate in a diabetes management program. Randomization will take place at the level of the patients in general practices. Trained practice nurses (case managers) will apply a case management program in addition to the diabetes management program. The case management intervention is based on the Guided Care model and includes six elements; assessing health care needs, planning care, create access to other care providers and community resources, monitoring, coordinating care and recording of all relevant information. Patients in the control group will continue their participation in the diabetes management program and receive care-as-usual from their general practitioner and other care providers.

**Discussion:**

We expect that the case management program, which includes better structured care based on scientific evidence and adjusted to the patients' needs and priorities, will improve the quality of care coordination from both the patients' and caregivers' perspective and will result in less consumption of health care services.

**Trial registration:**

Netherlands Trial Register (NTR): NTR1847

## Background

With the ageing of the population and the increase of prevalence rates of most chronic diseases at older age, increasingly more patients with a chronic disease also suffer from other chronic diseases [1]. In the Netherlands 25-50% of people with a chronic disease is diagnosed with one or more comorbid disorders [2,3]. For patients with type 2 diabetes (T2DM) this percentage is even higher, approximately 60% [4].

Comorbid type 2 diabetes (T2DM) patients can participate in several single-disease oriented disease management programs. Disease management programs are defined as 'systematic, population-based approaches to identify persons at risk, intervene with specific programs of care and measure clinical and other outcomes'. The main goal of disease management programs is to provide good quality care for a chronic disease and to guarantee a central role for the patient in managing the disease [5].

However, participating in multiple single-disease oriented programs in combination with regular primary care, may lead to fragmented care. In designing these programs insufficient attention is paid to the possible comorbid conditions which co-exist with an (index-) disease. Comorbid patients are therefore at risk for suboptimal treatment, unsafe care, inefficient use of health care services, unnecessary costs and consequently run higher risks for adverse events [3,6]. Case management is a possible model to counteract fragmented care for comorbid patients. It is an individualized care program which coordinates all care involved for patients enrolled in different single-disease management programs, who have to adhere to various treatment protocols. It draws on evidence-based optimal care for systematically managing all existing conditions in a patient, and is tailored to the individual patients' preferences [7,8].

There are promising results in a primary care setting from pilot tests on the effects of case management, in which an improvement of the quality of chronic care was observed, especially in the communication, goal setting, decision support, coordination among providers, and in reducing health care costs [8-12]. Recently, a study on the effectiveness of case management in the USA has shown improvement on the self-reported quality of health care for comorbid elderly [13].

To improve the care for comorbid T2DM patients in the Netherlands, we used the Guided Care Model (GC) to design a case management care program customized to the Dutch primary care setting. In the Netherlands, every resident is listed in a primary care practice. The General Practitioner (GP) acts as gatekeeper to secondary (specialized) care which is only accessible after referral. Our aim is to create a comprehensive tool for the general Practice Nurse (PN), which allows her to manage and coordinate the care the comorbid patient needs and to stimulate involvement of the patient in his care process. In this study, the PNs will be trained in conducting the case management program and will hereafter be called *case manager*.

### Theoretical framework

GC is developed in the USA and is based on the Chronic Care Model, a framework to guide quality improvement and disease management activities in the care for patients with a chronic disease [10]. GC combines the elements of the Chronic Care Model in practice and is designed to improve the quality of care and the quality of life for patients with multiple chronic conditions and complex health care needs [7,10].

GC consists of the following elements: assessing health care and well-being needs, communicating intervention possibilities, goal setting and decision support, monitoring and timely evaluation with the patient [10]. These elements intervene on three levels in the patients' care system, on the organizational or practice level (by using the above mentioned elements), on the level of the care provider (by using decision support), and on the level of the patient (by encouraging self management).

### Objective

The objective of this study is to establish the additional value of case management superposed on a diabetes management program, in terms of perceived quality of care, quality of care from the perspective of the GP, the health status of the patient, diabetes control, and health care utilization in T2DM patients with comorbidity.

## Methods/Design

### Design of the study

This study is a randomized controlled trial. T2DM patients with at least one comorbid chronic disease will be assigned to the control or intervention group. All patients participate in a diabetes management system (the Diabetes Care System (DCS), receiving structured diabetes care. In addition, participants in the intervention group will receive the case management intervention. The duration of the intervention is 12 months. The Medical Ethics Committee of the VU University medical centre in Amsterdam approved the study. Participants are allowed to enter the study after signed informed consent. Both the diabetes management program (as part of the usual care in the control group) and the case management intervention will be provided in the practice in which the patient is listed.

#### Description of the Diabetes Care System (DCS)

*The Diabetes Care System (DCS) *is a diabetes management program, which started in 1996 in the West-Friesland region of the Netherlands. By incorporating the Chronic Care Model, the system aims at providing comprehensive regional diabetes care, educating diabetes patients and supporting GPs in treating these patients. By now, nearly 6,500 T2DM patients are registered at the DCS. All receive an annual extended diabetes check-up at the specialized DCS additionally to the diabetes care by their GP according to the guidelines of the Dutch College of General Practioners [14]. The basic principles of the DCS are: the coordination of diabetes care, feedback to the GP and patient empowerment.

Each patient is invited annually by the DCS for a physical examination and diagnostic tests such as blood and urine analysis. In addition, the patient visits a diabetes nurse and a dietician for information and advice in order to improve the skills and confidence needed for self management. The patients are invited for follow-up visits when necessary.

The DCS coordinates the diabetes care between primary and secondary care. Using a centrally organized database, clinical information of patients is accessible to involved health care providers. Results of the annual examination are sent to the patient's GP who is responsible for the management of the patient, delegation of tasks to the PN and the 3-montly follow-up [15,16]. The GP receives feedback from the DCS based on the average results of his patients compared to all patients participating in the DCS.

### Study population

#### Practices

Practices delivering diabetes care in cooperation with the DCS are eligible for participation in this study if they employ a PN for diabetes care and are willing to house the case manager.

#### Patients

Eligible T2DM patients participate in the DCS and are known with at least one of the following comorbid conditions: chronic ischemic heart disease [angina pectoris, previous myocardial infarction, and heart failure], stroke, depression, rheumatoid arthritis, osteoarthritis of hip and/or knee, cancer, chronic obstructive pulmonary disease. The case manager will identify eligible patients from the electronic medical record based on ICPC-codes (International Classification of Primary Care) representing the included comorbid conditions (*see *table 1). Patients are allowed to enter this study when there is not already a case manager involved, when they are not suffering from a health problem which could lead to death within one year, are capable to give informed consent, to personally fill in questionnaires and have sufficient knowledge of the Dutch language.

**Table 1 T1:** International Classification of Primary Care codes of comorbid conditions.

Condition	Code										
**Cancer**	A79	B72	B73	B74	D74	D75	D76	D77	N74	R84	R85
	S77	T71	U75	U76	U77	W72	X75	X76	X77	Y77	Y78
**Chronic ischemic heart disease**	K74	K75	K76								
**Chronic Obstructive Pulmonary Disease**	R95										
**Depression**	P76										
**Osteoarthritis of hip and/or knee**	L89	L90									
**Rheumatoid arthritis**	L88										
**Stroke**	K90										

This table provides an overview of the ICPC-codes corresponding the included comorbid conditions.

ICPC: International Classification of Primary Care

### Randomization

Patients will be randomly assigned to the intervention or control group (*see *Figure 1). Patients in the control group will receive care from the DCS, their GP and PN. Patients in the intervention group will receive the case management intervention from the case manager in addition. All eligible patients in the participating practices will be invited to join the study. Reasons for non participation will be carefully registered.

**Figure 1 F1:**
[figure not shown]
**Design of the study**. The figure shows the design of the CasCo-study.

### Intervention

The case management program is designed to complement the diabetes management program and therefore is additional to the care from the DCS. The program involves six basic elements from the GC model intended to improve the quality of care for the patient, their access to care, and their capacity for self care, including assessing health care needs, planning care, create access to other care providers and community resources, monitoring, coordinating care and recording of all relevant information [10].

### Training

To execute the program properly, the case manager will be trained in assessing the patients' health care needs (step 1) and in creating a care plan based on the assessment (step 2). The case manager will have frequent contacts with the patient, GP and other care providers. Therefore the case manager will also receive training in motivational interviewing techniques and communication strategies, during a 4-day course and two coaching-on-the-job sessions from a trainer skilled in communication in health care. MI is a patient-centered counseling approach and is intended to help the patient make decisions, to facilitate the patient's participation in care, and to reconsider the patients' priorities with the patient. This method aims at collaboration between the case manager and the patient, using the patient's intrinsic motivation (willingness and motivation for self-care) and care for their autonomy [17,18]. Furthermore, recognizing and using different communication strategies in conversations will help the case manager in their contacts with the patient, GP and other care providers. Coaching-on-the-job will be executed by the trainer during two consults between the case manager and a patient. The trainer will provide feedback following each consult.

#### Description of the intervention: the Case Management Program

The case management program as applied in this study entails the following steps;

##### Step 1) Assessing the patients' health care needs

Before the assessment takes place, the case manager collects information about the patients' co-morbidities, treatments and advices, health care utilization and medication use in the electronic medical records. The initial assessment takes place with the patient in a face-to-face intake at the general practice, by using the Resident Assessment Instrument-Community Health Assessment (RAI-CHA). The RAI was originally designed as a minimum data set to assess the health status of nursing home residents by identification of problems in 18 areas that may need specific care planning [19]. The RAI-CHA provides a comprehensive overview of the patients' medical, functional, cognitive, affective, psychosocial, nutritional and environmental status. The identified problem areas guide the design of an individualized care plan with the intention to improve or maintain the functional health status.

##### Step 2) Start planning care

Together with the GP and the PN responsible for diabetes care, the case manager creates a provisional care plan. This plan is based on information from the assessment and currently provided care by the GP and PN. In case the patient's health problems results in complex care according to the GP, a multidisciplinary consultation with all relevant care providers will take place. Regular participants are the GP, PN, case manager and a representative of the DCS (a dietician or diabetes nurse).

##### Step 3) Discussing the interim care plan with the patient

In a second consultation, the case manager will discuss the provisional care plan with the patient. The case manager will give sufficient information as a result of which the patient will be able to make decisions related to care or managing the problems found. Also, the case manager will inform the patient about community resources relevant to the patients' needs. This results in a care plan suitable to the priorities and needs of the patient and becomes definite after a final review from the GP, PN and case manager.

The care plan includes self-management activities for the patient by setting goals in an action plan (e.g. regarding nutrition, physical exercise, use of medication, and self-monitoring) tailored to the patients' capacities.

##### Step 4) Communicating the care plan to all involved care providers

The care plan will be communicated to the involved care providers in order to coordinate the care. The case manager will not take over the care provided by the other care providers, but will inform them about the patient's care plan and explain the case manager's role.

##### Step 5) Monthly contact with the patient

The case manager will monitor the patient monthly by telephone to detect and address emerging problems regarding the implementation of the care plan and the patients' health status. If necessary, the case manager discusses these problems with the GP and takes appropriate action.

The case manager will review the patient's action plan and stimulate self-management by coaching the patient in achieving goals. The case manager will regularly update the patients' status and care plan using the notes from these contacts.

##### Step 6) Recording

During the intervention period, the case manager will record relevant changes in health status and all actions undertaken in the patients' electronic medical record.

### Control group

The patients in the control group continue participating in the DCS. In consequence, the care patients receive in this group is more extensive than usual care alone. They receive extended diabetes care from the DCS and usual care for diabetes (and the comorbid conditions) from their GP and PN. Care in this group may include the involvement of a PN, referral to other health care professionals, medication reviews, etcetera. These activities will be monitored and measured as part of our data collection. However, these patients do not participate in the case management program and therefore will not be supervised by the case manager.

### Measurements

Table 2 provides an overview of all measurements. Data will be collected using the patients' electronic medical record, postal questionnaires, and semi structured interviews.

**Table 2 T2:** Measurement scheme.

Variable	Instrument	baseline	3 months	12 months
**Primary outcome**				
a. quality of care perceived by patients	CQ-Index GP care PACIC	X X	X X	X X
**Secondary outcomes**				
b. quality of care perceived by GP	Quality Indicators			X
c. health status of the patient	SF-12	X	X	X
d. diabetes control	Hba1c (%)	X	X	X
e. health care utilization	Contacts with care providers	X	X	X
	Medication use (RAI-CHA)	X		X

**Feasibility**	Semi-structured interviews			X

This table provides an overview of the time schedule of all measurements and measures.

CQ-Index for GP care: Consumer Quality Index for GP care; GP: General Practitioner; HbA1c: glycated haemoglobin level; PACIC: Patient Assessment of Chronic Illness Care; RAI-CHA: Resident Assessment Instrument - Community Health Assessment; SF-12: Short-Form 12.

To get more insight into the factors favoring and hampering the implementation of the case management program, we will perform a feasibility check using semi-structured in-depth interviews and collect data via patient questionnaires.

We will interview four groups: 1) all case managers delivering the intervention, 2) the GPs in the participating practices, 3) the diabetes nurses of the DCS, as well as 4) a random stratified selection of 15 patients of the intervention group (both patients who indicated in their questionnaire having been exposed well and poorly to the case management program). The interviews will be recorded using a voice recorder.

### Outcome assessment

Primary and secondary outcome measurements are assessed at baseline, at 3 and 12 months. Interim analyses will be carried out three months after the baseline measurement. This analysis will be purely descriptive concerning changes in the quality of the received care according to the patient as a result of participation in the case management program.

#### Primary outcome measures

The quality of care as perceived by the patient, will be measured with the experience part of the multidimensional questionnaire Consumer Quality Index for GP care (CQ-Index)[20]. The CQ-Index is a standardized systematic way of measuring, analyzing and reporting clients' experiences in care. The 'tailored care' subscale includes 4 items, to be scored on a 4-point scale and has been shown to be reliable (Crohnbach's alpha = 0.84)[21].

Additionally we will use the Patient Assessment of Chronic Illness Care questionnaire (PACIC), a 20-item questionnaire which measures patient-reported quality of chronic illness care. It can be used to determine whether the received care is patient-centered, proactive, planned and includes collaborative goal setting; problem-solving and follow-up support [22].

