### Sample size

The required sample size for this study is calculated on the basis of the main outcome measure, the 'tailored care' subscale of the CQ-Index. Previous research showed mean baseline scores of 3.1 (SD 1.0) on a 5-point scale [20]. We expect a mean improvement of 0.4 in the intervention group and 0.1 in the control group (mean difference in improvement 0.3). Assuming a pooled SD of change of 0.75 (SMD = 0.40), we would need complete data for 98 patients in each group; given 80% power and a significance level of 5%. We will recruit 2 × 115 patients allowing a drop-out rate of 15% during follow-up.

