## Discussion

In this paper we describe the design of a randomized controlled trial of a case management program led by a trained PN, the case manager, for comorbid T2DM patients. The project will represent a first step in the evidence about the effectiveness of a primary care based case management program by studying the effectiveness in the Dutch primary care setting of a program which has been proven feasible and acceptable in the USA. By superposing this case management program on a diabetes management program, we will also be able to identify its additional value compared to a single disease oriented management program.

We expect that better structured care based on scientific evidence and adjusted to the patients' needs and priorities can improve the quality of care coordination from both the patients' and caregivers' perspective and can result in less consumption of health care services. Patients with more than one chronic condition might need support to coordinate their care arrangements. This is reflected by the choice for quality of care as perceived by the patient as the main outcome measure. When case management superposed on diabetes management is more effective than diabetes management alone, many patients will benefit from a better organized care, better health outcomes, and more efficient use of health care services. From a societal perspective, effective case management will lead to more efficient health care utilization, and consequently lower costs.

The major strength of this study is the close fit to the normal procedure in primary care practice and the not invasive character of the case management program. Experiments with case management as proposed in this study are a logical next step in pursuing optimal care for diabetics with comorbidity, with the knowledge that more than 60% of the diabetics have one or more comorbid disorders. Also, when people get older, the prevalence of chronic illnesses increases. Taking this into account, care for comorbid diabetics can become very complex to manage. The model of case management superposed on disease management for diabetics can be seen as exemplary and it will be worthwhile to apply the results - if positive - to other single-disease management programs for other chronic diseases.

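### The article lists two whole questionnaires as primary outcomes but names and powers one CQ-Index subscale as the main outcome, so the 12-month primary result can be read two ways

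*Protocol article*

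**What the plan says.** Four places in the Protocol article describe the primary outcome.

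- **Table 2, Primary outcome row.** Two instruments share the row, "CQ-Index GP care PACIC". Both are marked at baseline, 3 months and 12 months.
- **Primary outcome measures.** Patient-perceived quality of care "will be measured with the experience part of the multidimensional questionnaire Consumer Quality Index for GP care (CQ-Index)[20". The section describes the 'tailored care' subscale (4 items, reliability 0.84) but does not call it the primary outcome. It continues: "Additionally we will use the Patient Assessment of Chronic Illness Care questionnaire (PACIC), a 20-item questionnaire".
- **Sample size.** The calculation is "calculated on the basis of the main outcome measure, the 'tailored care' subscale of the CQ-Index". It uses one effect (a difference in improvement of 0.3), one SD of change (0.75), 80% power and a 5% level. No time point is attached to the effect.
- **Discussion.** The rationale refers to "the choice for quality of care as perceived by the patient as the main outcome measure", which is a construct without an instrument.

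On timing, Outcome assessment states: "Primary and secondary outcome measurements are assessed at baseline, at 3 and 12 months". It then says of the interim analysis at three months: "This analysis will be purely descriptive concerning changes in the quality of the received care according to the patient". Design of the study adds: "The duration of the intervention is 12 months".

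**The concern.** The term for the main outcome covers a four-item subscale in Sample size and a whole construct in the Discussion, while Table 2 and Primary outcome measures give primary status to two complete questionnaires. A reader cannot tell from the document which variable decides the trial.

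This matters most when the measures disagree. Suppose that at 12 months 'tailored care' shows no difference and PACIC does. Table 2 and Primary outcome measures would support reporting a positive primary result, while Sample size would support reporting a negative one. The trial's conclusion would depend on which section is cited. If success on either measure were accepted, the 5% in the sample size would no longer be the error rate of the primary conclusion.

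**Working it through.** **1. Does the stated sample size belong to one endpoint?**

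Inputs from Sample size: difference 0.3, SD of change 0.75 (standardised difference 0.40), 80% power, 5% level, 98 complete cases per group, 2 × 115 recruited, 15% drop-out. Sidedness is not stated.

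Formula: n per group = 2 (z for alpha + z for power)² × SD² / difference².

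- Two-sided 5%: 2 × (1.960 + 0.842)² × 0.75² / 0.3² = 98.1, which is 98 rounded or 99 rounded up. The stated 98 is reproduced.
- One-sided 5%: 77.3, rounded up to 78. This does not reproduce 98, so the level is evidently two-sided.
- Drop-out: 98 / 0.85 = 115.3, against 115 stated. This is reproduced to within one patient.
- Power at 98 per group: 0.80.

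The calculation therefore covers a single two-sided test of one variable at 5%.

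**2. Do the sections agree on that variable?**

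| Section | What is primary or main |
|---|---|
| Table 2 | CQ-Index and PACIC |
| Primary outcome measures | CQ-Index experience part, plus PACIC |
| Sample size | 'Tailored care' subscale only |
| Discussion | The construct, no instrument |

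Sample size fits neither of the first two rows: it leaves out PACIC and narrows the CQ-Index to one subscale.

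**3. What would the error rate be if either measure sufficed at 12 months?**

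Assume two tests at 12 months (one from the CQ-Index, one from PACIC), each two-sided at 5%, no true effect on either, and either one counted as success.

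- Independent tests: 1 − 0.95² = 9.75%.
- Correlated tests: 1 − P(|Z1| < 1.96 and |Z2| < 1.96), with Z1 and Z2 bivariate normal with correlation r.

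| Assumed r | Chance of at least one false positive |
|---|---|
| 0 | 9.75% |
| 0.5 | 9.1% |
| 0.7 | 8.3% |
| 0.8 | 7.8% |
| 0.9 | 7.0% |

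The document gives no correlation, so every r is an assumption. Two care-experience questionnaires completed by the same patients are unlikely to be independent, so the lower rows are the more plausible.

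**4. What would it cost to keep both as alternative primaries?**

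Assume the standardised difference of 0.40 also holds for PACIC, and split the level to 2.5% each. The same formula gives 118.8, rounded up to 119 complete cases per group, and 119 / 0.85 = 140 recruited per group. Power for each measure at 98 per group would be 0.71. The stated size fits only the single-endpoint reading.

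**The case against.** The best defence is that the sections form a sequence from construct to instrument to variable. The Discussion gives the construct, Primary outcome measures gives the instrument, and Sample size gives the variable, in the singular. 'Tailored care' is the only CQ-Index subscale that Primary outcome measures describes, and PACIC enters there as an addition. This is a fair account of what was probably intended, and it supports the fix below. It does not remove the conflict, because PACIC still has primary status under both primary-outcome headings, and nothing in the article ranks it below 'tailored care'.

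A second defence is that a condensed article may leave a testing hierarchy or a split of the 5% to a full protocol or analysis plan. That is correct, and the missing rule is not the point here. The point is that the article makes statements about what is primary that disagree, and any later plan would have to overrule one of them.

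A reader might also infer a larger problem: two instruments at two times would be four tests, with 1 − 0.95⁴ = 18.5% if independent, and more if every CQ-Index dimension were tested. The document does not support this.

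- Outcome assessment makes the three-month analysis descriptive, so it is not a stated route to success.
- The marks in Table 2 show when measurements are taken, not when hypotheses are tested.
- The 12-month intervention, and the contamination argument in the Discussion, which refers to the effect after 12 months, both point to 12 months as the time for inference.
- No section says that each CQ-Index dimension will be tested, and their number is not given.

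Nor does any section say that a positive result on either instrument is enough. The error rates above are therefore conditional.

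**Conclusion.** The point holds as a contradiction over the primary outcome at 12 months. One subscale was powered, and two questionnaires are labelled primary. Discordant results on 'tailored care' and PACIC would let the document support opposite conclusions.

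If either measure alone were accepted, the false-positive rate at 12 months would lie between 7.0% and 9.75% for correlations from 0.9 down to 0, against the intended 5%. This rests on assumed correlations and on an either-one-suffices rule that the document neither states nor excludes. The sample size is sound for the single endpoint named in its own section, so the defect lies in how the primary outcome is specified and not in the number of patients.

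**What to change.** - In Table 2 and in Primary outcome measures, state one primary outcome: the CQ-Index 'tailored care' subscale at 12 months, tested two-sided at 5%, to match Sample size.
- Move PACIC and the other CQ-Index scales to the secondary outcomes.
- In Sample size, state that the powered difference of 0.3 applies at 12 months and that the 5% is two-sided.

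Testing PACIC formally only if the primary is significant is one valid option, but the repair does not require it.

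The cost is wording. The 98 complete cases per group, the 2 × 115 recruited, the visits and the data collection all stay as they are. The downside is that PACIC loses primary status, although the trial was not powered on it.
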